## Abstract

**Objectives:**

The aim of this study is to gain experienced nursing perspective on current and future complication reporting and grading in Urology, establish the CAMUS CCI and quality control the use of the Clavien‐Dindo Classification (CDC) in nursing staff.

**Subjects and Methods:**

The 12‐part REDCap‐based Delphi survey was developed in conjunction with expert nurse, urologist and methodologist input. Certified local and international inpatient and outpatient nurses specialised in urology, perioperative nurses and urology‐specific advanced practice nurses/nurse practitioners will be included. A minimum sample size of 250 participants is targeted. The survey assesses participant demographics, nursing experience and opinion on complication reporting and the proposed CAMUS reporting recommendations; grading of intervention events using the existing CDC and the proposed CAMUS Classification; and rating various clinical scenarios. Consensus will be defined as ≥75% agreement. If consensus is not reached, subsequent Delphi rounds will be performed under Steering Committee guidance.

**Results:**

Twenty participants completed the pilot survey. Median survey completion time was 58 min (IQR 40–67). The survey revealed that 85% of nursing participants believe nurses should be involved in future complication reporting and grading but currently have poor confidence and inadequate relevant background education. Overall, 100% of participants recognise the universal demand for reporting consensus and 75% hold a preference towards the CAMUS System. Limitations include variability in nursing experience, complexity of supplemental grades and survey duration.

**Conclusion:**

The integration of experienced nursing opinion and participation in complication reporting and grading systems in a modern and evolving hospital infrastructure may facilitate the assimilation of otherwise overlooked safety data. Incorporation of focused teaching into routine nursing education will be essential to ensure quality control and stimulate awareness of complication‐related burden. This, in turn, has the potential to improve patient counselling and quality of care.

## INTRODUCTION

1

Despite remarkable advancements in surgical care and technology, routine morbidity and mortality audits and a growing tendency to practice defensive medicine, the risk of iatrogenic and surgery related adverse events remain high.^1^ The majority of these surgical complications are deemed preventable and often receive great scrutiny due to modern safety expectations.^2^, ^3^ While complication reporting and grading, to varying extents, has been implemented into practice by surgeons for many years,^4^, ^5^, ^6^, ^7^ nursing staff are often less involved in structured complication reporting and grading. Rather, the process of incident reporting (e.g., Critical Incident Reporting System [CIRS]), which was introduced to improve patient care and expand a hospital's safety infrastructure, is routinely incorporated and documented in postoperative care.^8^, ^9^

Comprehensive complication reporting and grading in the postoperative period by all healthcare personnel (including nurses, surgeons and critical care specialists) will result in a more holistic assessment of a hospital's safety framework. In particular, a uniform classification system and database for nurses and surgeons would ensure thorough and accurate reporting and grading of complication‐intervention events.^10^, ^11^

Current and pre‐existing complication systems (e.g., Clavien‐Dindo Classification [CDC],^4^ Comprehensive Complication Index [CCI],^6^ Bern CCI,^7^, ^12^ and Common Terminology Criteria for Adverse Events [CTCAE]^13^) are inherently flawed as they only account for the severity of complication‐intervention events but fail to consider and incorporate nursing insight and perception of patient burden into the reporting of complications. As such, in addition to the original Delphi study^14^ involving urologists, anaesthetists and intensive care physicians, the Complication After Major & Minor Urological Surgery (CAMUS) Collaboration has launched a second Delphi study targeting nursing staff opinion.^15^

The aim of this study is to gain experienced nursing perspective on current and future complication reporting and grading in Urology, establish the CAMUS CCI and quality control the use of the CDC in nursing staff. Nursing involvement has the potential to improve efficiency and accuracy of complication reporting and grading in centres worldwide, ensure minor interventions are not underappreciated and may, in turn, enhance their own insight into the spectrum, and consequences, of perioperative and postoperative complications.

## SUBJECTS AND METHODS

2

The Delphi method has been increasingly used for developing consensus guidance on best practice.^16^, ^17^, ^18^, ^19^ The primary intent of the Delphi method is to address and explore clinical areas where high‐quality evidence is limited, thereby instead reaching consensus through expert and best practice opinion. The steps involved in this process will be outlined further in the study approach (see Figure S1). In brief, (i) a group of expert participants will be questioned about the issue of interest; (ii) the process is anonymous in order to avoid social pressure and conformity to a dominant view (‘bandwagon effect’); (iii) the procedure is iterative in nature, comprising several rounds of enquiry and (iv) the design of subsequent rounds is informed by a summary of the group response of the previous round. It can be tailored to the requirements of the individual research objective, ranging from open and exploratory to standardised confirmatory approaches.^20^

The original Delphi study aimed to create a standardised and reproducible assessment of perioperative complications and overall associated morbidity by introduction of the CAMUS Reporting and Classification System (see Table S1).

In this novel nurse targeted pilot Delphi study, we aim the following (see Table 1):
Evaluate nursing opinion on current and future involvement and interest in complication reporting (formal/informal) and grading.Have nursing participants assess the severity of various complication‐intervention events using a 0–100 scale (i.e., proposed CAMUS Grade) which will later be used to develop and validate the CAMUS CCI.Quality control the use of the CDC by nursing staff, clarify areas for improvement and requirements for future involvement and assess the need for further education in nurses.Gather nursing opinion on the appropriate detail and complexity required for a useable complication reporting and grading system (i.e., CAMUS supplemental grades).

**TABLE 1 bco2173-tbl-0001:** Nurse Delphi study aims

#	Aims
1	Evaluate nursing opinion on current and future involvement and interest in complication reporting (formal/informal) and grading.
2	Have nursing participants assess the severity of various complication‐intervention events using a 0–100 scale (i.e., proposed CAMUS Grade) which will later be used to develop and validate the CAMUS CCI.
3	Quality control the use of the CDC by nursing staff, clarify areas for improvement and requirements for future involvement, and assess the need for further education in nurses.
4	Gather nursing opinion on the appropriate detail and complexity required for a useable complication reporting and grading system (i.e., CAMUS supplemental grades).

### Study approach

2.1

An outline for the nurse Delphi study approach including the method selection of nominated expert participants, invitations and reminders to participants, sample size and response rate, defining and achieving final consensus and Steering Committee selection can be seen in Table 2 (A).

**TABLE 2 bco2173-tbl-0002:** Study method

A: Study approach		
#	Section	Question
1	Delphi method	11 steps of the Delphi Study (see Figure 1a).
2	Selection of nominated expert participants	Certified local and international inpatient and outpatient nurses specialised in urology, perioperative nurses (i.e., anaesthetic nurses, recovery nurses), and urology‐specific advanced practice nurses/nurse practitioners will be invited to complete the survey. Primarily urology‐experienced perioperative nurses will be targeted (not required for inclusion).
3	Invitations and reminders to Delphi participants	Participant experts will be contacted via email (obtained via CAMUS databases and trial coordinators) and word of mouth. All participants will be invited to complete all Delphi rounds. Round 1 will be closed after 12 weeks. Reminders will be sent every 7–14 days.
4	Sample size and response rate for the Delphi Study	Minimum sample size of 250 participants will be targeted. In case of withdrawal, participants will be contacted to identify reason for withdrawal.
5	Defining and achieving final consensus	Consensus will be defined, a priori, as majority agreement (75% or greater) of participant response. If consensus is not reached then subsequent Delphi rounds (minimum of 2, maximum of 5) will be performed under guidance of the Steering Committee.
6	Steering Committee selection	Committee members will be selected primarily from our team of investigators, as well as several highly experienced specialists (nurses, urologists, critical care physicians and methodologists) in surgical reporting and grading. The selected committee will prepare and provide group feedback to participants, as well as rectify outstanding items, or add new items, if consensus is not achieved.

B: Description, content, aims and rationale of the 12 parts of the Nurse Delphi Survey		
Part	Description	Content, aims and rationale
1	Participant demographic details	Basic participant demographic information (e.g., age, location, experience) to assist in quality assurance.
2	Complication reporting and grading; now and in the future	Information regarding institutional‐driven complication reporting and grading, gauging degree of participant experience in reporting and grading, and opinions on current and potentially future nursing involvement in complication reporting & grading.
3A	Grading intervention events – CAMUS Classification	Obtain consensus on severity of a wide range of complication‐intervention events using the new CAMUS Classification.
3B	Grading intervention events – Clavien‐Dindo Classification (CDC)	Obtain consensus on severity of a wide range of complication‐intervention events using the CDC, the current standard for grading complications.
3C	Rating scenarios	Range of various scenarios requiring consensus that aim to challenge current perceptions of complication reporting, highlight pitfalls and complexities of the CDC, and finally consider potential solutions, updates, and ultimately reach consensus.
3D	CAMUS extended grade	Introduction and opinion of the new ‘CAMUS extended grade’ (see Table 1).
3E	CAMUS intra‐operative grade	Introduction and opinion of the new ‘CAMUS intra‐operative grade’ (see Table 1).
3F	CAMUS post‐operative grade	Introduction and opinion of the new ‘CAMUS post‐operative grade’ (see Table 1).
3G	CAMUS disability adjunct grade	Introduction and opinion of the new ‘CAMUS disability adjunct grade’ (see Table 1).
3H	Supplemental CAMUS grades – summative example and opinion	Provides a summative example of all the supplemental grades, as described above, to show its clinical and practical applicability.
4	Grading scenarios	Practical ‘multi‐intervention’ scenarios as a supplement to PARTS 3A‐G and aim to clarify which specific events, and the overall number of intervention events, people would consider reportable for each scenario.
5	Participant identification and consent	Requests the full name, preferred title, and professional affiliations of each participant performing the nurse Delphi survey for quality assurance and will further ensure participants are compensated for their time with PubMed listed collaborative authorship.

Individuals will be selected based on experience and presumed knowledge of surgical outcomes. Participants invited to complete the survey are local and international inpatient and outpatient nurses specialised in urology, perioperative nurses (i.e., anaesthetic nurses and recovery nurses) and urology‐specific advanced practice nurses/nurse practitioners. Our assumption is that any certified nurse will have a reasonable amount of experience in perioperative and postoperative care and can hence judge on severity of adverse surgical outcomes and complication‐intervention events during their hospital stay or mid‐ to long‐term follow‐up.

Delphi participants identified will initially be contacted using emails obtained from the CAMUS Collaboration database, Urological nursing associations and word of mouth. Participants will also be encouraged to invite their peers to participate, utilising the ‘snowball sampling’ approach to increase sample size.

All participants will be invited to complete each Delphi round, unless they withdraw at any stage. Consent will be assumed if participants complete and submit the survey. Email reminders will be sent to all primary selected participants every 14 days following survey distribution. Round 1 will close after 12 weeks.

No standard limit on when a question is considered to have reached consensus exists.^21^, ^22^ Ideally, consensus between participants over 90% would give substantial confidence that agreement is reached; however, this threshold may require additional Delphi rounds which is neither practical nor necessary. As such, in agreement with our original Delphi study,^14^ consensus will be defined as majority agreement (75% or greater) of participant response.^23^

Prior to finalising the nurse Delphi survey, a pilot survey run with 20 participants (*n* = 20 based on previous author Delphi experience) was performed in December 2021 to ensure comprehension, receive final feedback and gauge duration and functionality of the survey.^18^, ^23^ The 20 participants, all of whom met inclusion criteria, were recruited via international centres involved in the CAMUS Collaboration by personalised email, and a variety of experienced inpatient and outpatient nurses were targeted to ensure cohort diversity. The number 20 was chosen based on author experience from the original Delphi study,^14^ which yielded meaningful data and general feedback that enhanced the overall survey quality prior to its final release.

Ethics approval for this study was obtained Epworth ID: EH2021‐708, and the study was registered on ClinicalTrials.gov PRS (NCT05272592).

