Yes; grading	4 (20)
Yes; both	0 (0)
No	16 (80)
Importance of a consensus paper to clarify complication in Urology from nursing perspective	
Yes	17 (85)
No	3 (15)

C: Grading various intervention events using the proposed CAMUS Grade and CDC^b^								
Intervention‐event	CAMUS Grade* Median (IQR*)*	Clavien‐Dindo Classification (CDC)^c^ *N* (%)						
	CAMUS [0–100]	No complication	CDC1	CDC2	CDC3a	CDC3b	CDC4a	CDC4b
IDC insertion (LA)	26.5 (25–40) (6.25–13.75)	0 (0)	2 (10)	12 (60)	5 (25)	1 (5)	0 (0)	0 (0)
SPC insertion (LA)	40 (35–50)	0 (0)	1 (5)	9 (45)	9 (45)	0 (0)	1 (5)	0 (0)
SPC insertion (GA)	50 (35–75)	0 (0)	1 (5)	0 (0)	3 (15)	15 (75)	0 (0)	1 (5)
Intermittent self‐catheterisation (ISC)	31.5 (28–35)	0 (0)	3 (15)	13 (65)	4 (20)	0 (0)	0 (0)	0 (0)
Clot evacuation in theatre (GA)	50 (45–66.25)	0 (0)	0 (0)	1 (5)	1 (5)	17 (81)	0 (0)	1 (5)
Repair of bladder perforation (GA)	70 (60–85)	0 (0)	0 (0)	0 (0)	0 (0)	17 (81)	1 (5)	2 (10)
Flexible cystoscopy + dilatation (LA)	35 (30–55)	0 (0)	0 (0)	8 (40)	11 (55)	1 (5)	0 (0)	0 (0)
Stent migration requiring re‐stent (GA)	45 (39–57.5)	0 (0)	1 (5)	0 (0)	1 (5)	18 (90)	0 (0)	0 (0)
Nephrostomy insertion (LA)	35 (35–53.75)	0 (0)	1 (5)	0 (0)	18 (90)	1 (5)	0 (0)	0 (0)
Nephrostomy exchange (LA)	25 (20–30)	0 (0)	9 (45)	4 (20)	5 (25)	1 (5)	0 (0)	1 (5)
VAC dressing (GA)	50 (35–57.5)	0 (0)	0 (0)	1 (5)	0 (0)	18 (90)	1 (5)	0 (0)
Oral antibiotics	20 (12–28.75)	0 (0)	5 (25)	15 (75)	0 (0)	0 (0)	0 (0)	0 (0)
IV antibiotics	25 (22–51.25)	0 (0)	1 (5)	18 (90)	0 (0)	1 (5)	0 (0)	0 (0)
Packed red cell transfusion	23 (21–67.5)	0 (0)	0 (0)	18 (90)	0 (0)	0 (0)	1 (5)	1 (5)
HDU admission	50 (45–75)	0 (0)	0 (0)	2 (10)	1 (5)	1 (5)	16 (80)	0 (0)
ICU admission	77.5 (65–90.75)	0 (0)	0 (0)	0 (0)	0 (0)	2 (10)	16 (80)	2 (10)
Physiotherapy (pelvic floor training) for incontinence	10 (9.25–15)	1 (5)	19 (95)	0 (0)	0 (0)	0 (0)	0 (0)	0 (0)
Ultrasound‐guided aspiration of lymphocele WITHOUT drain insertion (LA)	31 (30–38.75)	0 (0)	1 (5)	7 (35)	11 (55)	1 (5)	0 (0)	0 (0)
Ultrasound‐guided aspiration of lymphocele WITH drain insertion (LA)	12.5 (10–20)	0 (0)	0 (0)	6 (30)	13 (65)	0 (0)	1 (5)	0 (0)
Sodium bicarbonate (acute)	8 (8–25)	1 (5)	17 (85)	2 (10)	0 (0)	0 (0)	0 (0)	0 (0)
Sodium bicarbonate (lifelong)	15 (12–41.5)	1 (5)	17 (85)	1 (5)	1 (5)	0 (0)	0 (0)	0 (0)
NGT insertion on ward for ileus	30 (23–35)	0 (0)	10 (50)	8 (40)	0 (0)	2 (10)	0 (0)	0 (0)
Total parental nutrition (via PICC) (TPN)	31 (28–61.25)	0 (0)	1 (5)	14 (70)	4 (20)	0 (0)	0 (0)	1 (5)

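### The CDC-use component of Aim 3 is judged only by agreement between nurses, which shows reproducibility but not correct use; a reference grade and a Round 1 accuracy summary should be fixed

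*Protocol article*

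**What the plan says.** Aim 3 (Subjects and Methods, Table 1) reads in part: "Quality control the use of the CDC by nursing staff, clarify areas for improvement and requirements for future involvement". Its last element is to "assess the need for further education in nurses".

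Table 2 (B) describes Part 3B, the part in which nurses assign CDC grades. The entry opens "Obtain consensus on severity of a wide range of" complication-intervention events and ends "events using the CDC, the current standard for grading complications". Part 3A, which introduces the new CAMUS scale, has almost the same stated purpose.

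Table 2 (A), row 5, sets one success criterion for the whole survey: "Consensus will be defined, a priori, as majority agreement (75% or greater) of participant response". It continues: "If consensus is not reached then subsequent Delphi rounds (minimum of 2, maximum of 5) will be performed". Row 6 adds: "The selected committee will prepare and provide group feedback to participants, as well as rectify outstanding items", or add new items, where consensus is not achieved. Subjects and Methods also says that a summary of one round's group response informs the design of the next.

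Table 3 (C) gives the pilot CDC answers as counts per grade. Neither that table nor the Results text mentions a correct grade, a scoring key or an error rate.

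**The concern.** The CAMUS grade is new, so asking a panel to converge on severity is a reasonable use of the Delphi method. The CDC is different: the article itself treats it as the existing standard. Quality control of how people apply an existing standard calls for a comparison with that standard. As described, Part 3B compares nurses only with each other.

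Two consequences follow for the CDC-use component of Aim 3. First, an event on which most nurses share the same mistake would count as settled. The pilot makes shared error plausible: 15 of 20 participants had never graded a complication and 4 of 20 had encountered no grading system (Table 3 (B)). Second, if Part 3B events enter a later round, nurses will answer after group feedback. Agreement measured then partly reflects the feedback and is a poor guide to how nurses use the CDC unaided.

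**Working it through.** The article gives no figure for CDC accuracy, so there is none to reproduce. The check asks what the stated criterion can show, using the pilot counts in Table 3 (C).

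**1. Pilot agreement.** There are 25 events and 7 answer categories, and each row of counts sums to 20. For each event, agreement = largest count / 20, compared with 0.75.

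- At or above 75%: 16 of 25 events. Two sit exactly on 15/20 = 75%: SPC insertion under GA, and oral antibiotics.
- Below 75%: 9 of 25 (36%), as follows:

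| Event | Largest share on one grade |
|---|---|
| IDC insertion (LA) | 60% |
| SPC insertion (LA) | 45% (tied, CDC2 and CDC3a) |
| Intermittent self-catheterisation | 65% |
| Flexible cystoscopy + dilatation (LA) | 55% |
| Nephrostomy exchange (LA) | 45% |
| Lymphocele aspiration without drain | 55% |
| Lymphocele aspiration with drain | 65% |
| NGT insertion for ileus | 50% |
| Total parenteral nutrition | 70% |

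Two rows (clot evacuation, repair of bladder perforation) print 17 (81), but 17/20 = 85%. Both percentages exceed 75%, so the 16/9 split does not change.

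**2. Chance-corrected agreement.** Fleiss kappa = (P_o − P_e)/(1 − P_e).

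- P_o is the mean over events of (Σ count² − 20)/(20 × 19) = 0.621.
- The column totals over 500 answers are 3, 89, 139, 87, 131, 39 and 12, so P_e = Σ(total/500)² = 0.215.
- Kappa = (0.6208 − 0.2146)/(1 − 0.2146) = 0.517.

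**3. What agreement says about correctness.** Let a be the share choosing the most common grade, and suppose one grade is correct. If the most common grade is correct, the share correct is a. If it is not, the share correct is at most 1 − a. At a = 0.75 the two values are 75% and at most 25%. The 75% rule treats these cases alike. For SPC insertion (LA), 9 of 20 chose CDC2 and 9 of 20 chose CDC3a. The counts show that the event is problematic, but not which group applied the CDC as defined.

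**4. What Round 1 could deliver with a reference grade.** The 95% half-width is 1.96 × √(p(1 − p)/n), with n = 250 from Table 2 (A), row 4, independent responses and all 250 answering the event:

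- p = 0.50: ±6.2 points
- p = 0.75: ±5.4 points
- p = 0.90: ±3.7 points

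The target sample is therefore adequate for an accuracy summary per event. Snowball recruitment could make responses correlated and widen these intervals somewhat; the article gives no figure from which to quantify that.

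**The case against.** A reader might infer that the study cannot answer Aim 3. The documents do not support that. Round 1 grades are given before any group feedback, and later rounds do not erase them, so they can be scored against a reference without new items or more participants. Nor does all of Aim 3 depend on an error rate. Part 2 asks directly about training, confidence and involvement, and the article draws its education conclusion from those answers (17 of 20 reported no adequate training, 14 of 20 no current confidence).

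A reader might also infer that failed Part 3B events will be re-asked unchanged and that Aim 3 will be reported from later rounds, making CDC use look better than it is. Neither is stated. Further rounds come from a general rule, under which outstanding items may be rectified or new ones added. What stands is narrower: Part 3B is described as a consensus exercise and is not exempted from that rule.

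Agreement is also a legitimate part of quality control. The Discussion names inter-rater variability as a concern, and an even split on an event flags an area for improvement. Agreement is incomplete here, not irrelevant.

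The items are bare intervention labels and the CDC definitions are not reproduced, so one correct grade per event cannot be assumed. That is a reason to allow sets of acceptable grades, not a reason to do without a reference.

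Finally, the article condenses a fuller protocol in which a key might exist, so the mere absence of a scoring key is not the point. The point is that the purpose and criterion the article does state for Part 3B do not fit an aim of quality control.

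**Conclusion.** The point holds for the CDC-use component of Aim 3 and no further. As described, that component is judged only by agreement between nurses, and agreement cannot separate correct from incorrect use. If the pilot pattern carried over to Round 1, 16 of 25 events (64%) would count as settled with no check of the grade, and 9 of 25 (36%) would fall under the rule for further rounds. Any agreement measured after feedback would partly reflect the feedback.

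This rests on two assumptions: that quality control of the CDC means, at least in part, use in line with its definitions, and that the general consensus rule applies to Part 3B because no exemption is given. The 16/9 split comes from 20 pilot participants and is only a guide to Round 1. The other parts of Aim 3 are unaffected, and the gap can be closed on data already to be collected. Severity: should-fix.

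**What to change.** Before Round 1 data are seen, the Steering Committee locks a reference CDC grade for each Part 3B event, or a set of acceptable grades where the bare label is ambiguous. It should work from the CDC definitions and not from the most common pilot answer.

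Define the CDC-use outcome of Aim 3 as percent correct per event with a 95% confidence interval, plus the shares over-graded and under-graded, from Round 1 (pre-feedback) responses only. Keep kappa as a secondary measure of reproducibility. State that neither the 75% rule nor later rounds serve as the measure of CDC use, and reword the Part 3B purpose in Table 2 (B) to match.

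The cost is one committee session and a short analysis, with no new items and no larger sample. The drawback is that some events will carry more than one acceptable grade, which makes percent correct less demanding for those events; they should be marked in the report.

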**FIGURE 1 bco2173-fig-0001:**
[figure not shown]
Stakeholders that benefit from a standardised complication reporting system. If the CAMUS Reporting and Classification System can be implemented worldwide, after calibration, it has potential to create reliable guidelines and recommendations, and provide benefit to all potential stakeholders (i.e., nursing staff, surgeons, units, hospitals, patients, family members/next of kin, researchers, health insurance companies, politicians and urological organisations)

This Delphi study and proposed CAMUS System has several limitations including (i) variability in nursing experience, (ii) complexity of supplemental CAMUS grades, (iii) dependency on honesty, (iv) time‐consuming nature of comprehensive and accurate complication reporting, (v) risk of poor data due to participant fatigue and withdrawal (despite compensatory authorship being offered) and (vi) lack of randomisation in the nurse Delphi survey questionnaire.

However, to the best of our knowledge, although nurses have previously been involved in the formulation of complication grading tools, this is the first ever complication reporting system developed with a consideration for nursing staff insight and opinion. This insight will provide an added dimension to the understanding of patient burden.

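### Later-round consensus is a share of whoever responds, so an item near 75% can cross the line because dissenters leave, and the plan has no rule to tell this from changed opinion

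*Protocol article*

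**What the plan says.** Table 2 (A), row 5, fixes the decision rule: "Consensus will be defined, a priori, as majority agreement (75% or greater) of participant response". The running text of section 2.1 repeats it: "consensus will be defined as majority agreement (75% or greater) of participant response". Neither place gives a different rule, or a different denominator, for rounds after the first.

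On who is asked again, section 2.1 says: "All participants will be invited to complete each Delphi round, unless they withdraw at any stage". On the number of rounds, Table 2 (A) says: "If consensus is not reached then subsequent Delphi rounds (minimum of 2, maximum of 5) will be performed under guidance of the Steering Committee".

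On size and loss, row 4 of the same table says: "Minimum sample size of 250 participants will be targeted", and then: "In case of withdrawal, participants will be contacted to identify reason for withdrawal". The 250 is not tied to any particular round. Reminders are planned in both the table and the text. The limitations in section 4 name the "risk of poor data due to participant fatigue and withdrawal (despite compensatory authorship being offered", without a rate.

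**The concern.** A Delphi study claims that agreement rises because participants see the group's answers and reconsider. Under a share-of-responders rule, two different events give the same reported result: dissenters change their minds, or dissenters stop answering. Only the first is convergence.

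Selective loss is plausible here. The authors expect fatigue and withdrawal, and the Steering Committee feeds group results back between rounds, so a dissenter may learn that they are in the minority. Items near the line are also realistic. In the pilot (Table 3, n = 20, so imprecise), a surgeon's obligation to give patients outcome data and the description of the complication each stood at 14/20 = 70%. Reporting of rehabilitation for general deconditioning stood at 15/20 = 75%.

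At stake is whether an item reported as nursing consensus is one that the panel as first surveyed supports at the stated level. The article says the study's outcomes will feed the CAMUS CCI.

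**Working it through.** **Inputs.** The threshold is 75% of responses (Table 2 (A) and section 2.1). The Round 1 panel is taken as 250, the stated minimum; this is an assumption, because the article does not tie 250 to a round. Retention by opinion is not given and is varied below. The 250 comes without precision, power or attrition inputs, so there is no figure of the plan's own to reproduce.

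**Only dissenters leave, no answer changes.** With A agreers and D dissenters in Round 1, and k dissenters lost, agreement is A/(A + D − k). This reaches 0.75 when k ≥ D − A/3.

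| Round 1 agreement | A / D | D − A/3 | k needed | Share of panel | Later result |
|---|---|---|---|---|---|
| 74% | 185 / 65 | 3.3 | 4 | 1.6% | 185/246 = 75.2% |
| 72% | 180 / 70 | 10 | 10 | 4.0% | 180/240 = 75.0% |
| 70% | 175 / 75 | 16.7 | 17 | 6.8% | 175/233 = 75.1% |
| 68% | 170 / 80 | 23.3 | 24 | 9.6% | 170/226 = 75.2% |
| 60% | 150 / 100 | 50 | 50 | 20.0% | 150/200 = 75.0% |

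**Both groups lose members.** With retention rA and rD, agreement is A·rA/(A·rA + D·rD). From Round 1 agreement p, it reaches 75% when rD/rA ≤ p/[3(1 − p)]: 0.70/0.90 = 0.78 from 70%, and 0.72/0.84 = 0.86 from 72%. For a 70% item:

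- 90% vs 70% retained: 157.5/210 = 75.0%, crosses.
- 85% vs 65%: 148.75/197.5 = 75.3%, crosses.
- 80% vs 60%: 140/185 = 75.7%, crosses.
- 90% vs 80%: 157.5/217.5 = 72.4%, does not cross.
- 80% vs 80%: 140/200 = 70.0%, no drift.

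**Loss unrelated to opinion.** By the hypergeometric distribution, a 70% item reaches 75% by chance with probability 0.0007 if 200 of 250 remain and 0.018 if 150 remain. For a 74% item the probabilities are 0.29 and 0.33. That is sampling noise rather than drift, but the rule cannot recognise it either.

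**Opposite direction.** For an item at 190/250 = 76%, the loss of 11 agreers gives 179/239 = 74.9%, below the line.

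**What a paired display would show.** If 17 dissenters leave a 70% item, agreement among the 233 who answered both rounds is 175/233 = 75.1% in both, so there is no rise. Over all Round 1 responders, with leavers' answers carried forward, it stays 175/250 = 70.0%.

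**The case against.** Counting each round's responses is a common and defensible Delphi rule, and it contradicts nothing else in the article. Withdrawal is disclosed as a limitation, all 20 pilot participants finished, and an attrition analysis may sit in a fuller document not shown here. This stands in part. The point does not depend on a missing analysis, however: the decision rule is published here and labelled a priori, and as published it does not separate changed opinion from a changed panel.

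The direction of loss is also assumed. Many items are not votes for or against CAMUS, and a nurse may be in the majority on one and the minority on another. That stands. A reader might infer that attrition will push items towards consensus generally; the article offers no evidence for that.

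Other stronger readings also fail:

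- *Authorship is the only safeguard.* Reminders and contact about withdrawal are planned too, although neither changes the denominator.
- *Each later round costs another 58 minutes.* That median is for the complete pilot survey. Table 2 (A) has the committee deal with unsettled or new items, which suggests shorter later rounds.
- *The panel shrinks by a fixed fraction every round.* Those who merely skip a round are invited again.
- *One open item forces two extra rounds.* The wording on 2 to 5 rounds can also be read as a total.

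Finally, carrying leavers' answers forward freezes their views and can penalise real convergence. Suppose 200 of 250 stay on a 70% item at equal retention (140 vs 60) and 10 truly change. The round shows 150/200 = 75.0%, paired agreement rises from 70.0% to 75.0%, yet the carried-forward figure is (150 + 35)/250 = 74.0%. This is a good reason not to make that figure a condition of consensus.

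**Conclusion.** The point holds as a weakness of the stated rule, confined to items near the threshold. An item starting at 70% to 74% can be labelled consensus after the loss of 17 down to 4 dissenters from a panel of 250, with no changed answer. Further from the line it takes much more: half of all dissenters from 60%.

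The result rests on three assumptions: that each round's responders are the denominator, which is the natural reading but is not spelled out round by round; that Round 1 has 250 responders to the item; and that dissenters leave more readily than agreers. Without the third there is no systematic drift, and with the reverse the rule understates agreement. The article does not show that false consensus will occur. It fixes a rule under which false consensus could not be seen. That calls for added reporting, not a different threshold.

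**What to change.** Keep the 75% rule. For every item carried forward with unchanged wording, link answers across rounds by a coded study ID and report beside that round's result:

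- (a) Round 1 and later-round agreement among participants who answered the item in both rounds;
- (b) as a sensitivity analysis, agreement over all Round 1 responders to the item, with leavers' last answers carried forward.

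Flag as *consensus not robust to attrition* any item that reaches 75% only on the current responders, or without a rise in paired agreement. Items that the committee rewords fall outside this check and should be identified as such.

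Also state whether the limit of 2 to 5 counts total rounds or rounds after the first.

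The cost is wording and a little more analysis. Linkage looks feasible, because Part 5 of the survey already collects names and REDCap distributes the rounds. The downside is that some items near 75% will carry a caveat, including a few, as in the 74.0% example above, where the change of opinion was real. Showing (a) beside (b) lets readers see which case applies.
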